### Randomization and study visits

Subjects will attend the clinic for a regular visit and blood draw. After a careful review of their medical history patients who fulfill the inclusion criteria will be contacted and informed about the study protocol. Patients who agree to participate in the study will be invited to a further blood work-up to ensure that metabolic acidosis is chronic rather than a one-time imbalance of the acid–base status. After obtaining written informed consent (day 0) each patient will be randomized 1:1 either to the treatment group or the control group (Figure 1). Subjects will be stratified for age >60 years and ≤60 years [34], presence of diabetes mellitus (yes/no) [35], severe chronic metabolic acidosis (serum HCO_3_^-^ <18 mmol/L) versus moderate metabolic acidosis (serum HCO_3_^-^ ≥18 mmol/L), and for previous alkali treatment (yes/no). Previous alkali treatment is defined as being continued for longer than 6 months (>25% of the treatment period of the planned study) and serum HCO_3_^-^ ≥20 mmol/L on more than 75% of measurements. Stratified randomization will be carried out using the web-based randomizer program provided by the Medical University of Vienna [https://www.meduniwien.ac.at/randomizer/web/login.php]. We use the minimization method with a preferred treatment probability of 0.9, and a combination depth of 2.0, to guarantee that treatment allocation is balanced in all levels of the stratification factors, as well as in all pairwise combinations of stratification factors. After randomization, subjects will receive either the high dose of sodium bicarbonate or, if necessary, a low-dose rescue therapy with sodium bicarbonate.

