### Statistical methods

The intention-to-treat population will be used for statistical analysis. The primary analysis focuses on the estimated treatment effect at 2 years (difference between the two groups in eGFR after two years), which will be provided as the point estimate at the expected difference, 95% confidence interval and *P*-value. Mortality of patients or other reasons for dropout will be addressed by jointly modeling longitudinal eGFR and time to death using an appropriate joint model for longitudinal and time-to-event outcome [37]. In the longitudinal part of this model, a linear mixed model will be used with the repeated eGFR measurements as outcome values, and including as fixed factors treatment group, all stratification criteria (age, diabetes, severity of acidosis, previous alkali treatment), the eGFR baseline value and time since start of treatment, and a random intercept. An interaction effect (product term) of the treatment group and the time since start of treatment will also be included. Graphical diagnostic tools (residual plots) will be used to confirm the adequacy of model assumptions. A secondary outcome is time to death, compared between the treatment groups, which will also be estimated by the joint modeling approach. The time up to the point of need of RRT will be compared between the two treatment groups, accounting for death as a competing risk, by modeling the cumulative incidence function [38], including treatment group and the covariates age, diabetes, severity of acidosis and baseline eGFR. Percent change (from baseline to week 20 and baseline to week 104, respectively) in markers of bone metabolism will be analyzed by analysis of covariance, to adjust for sex, age, change in renal function, and baseline values of the bone markers. The incidence of serious adverse events will be reported and compared between groups using the chi-squared test. Baseline parameters (etiology of CKD, relevant medical disease, age, gender, concomitant medication, blood pressure, number of antihypertensive medications, and laboratory measurements) will be analyzed descriptively for the interventional and control group, respectively. SAS (Version 9.3, SAS Institute Inc., Cary, NC, USA, 2011) will be used for data management and analysis, and R 2.12.2/package JM [37] will be used for the main outcome analysis.

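### The bone-marker ANCOVA carries only one of the four minimisation factors and the RRT model three, while the primary model carries all four: a minor inconsistency in two secondary analyses

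*Protocol article*

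**What the plan says.** Under Randomization and study visits, the protocol article names four factors: "Subjects will be stratified for age >60 years and ≤60 years", "presence of diabetes mellitus (yes/no"), "severe chronic metabolic acidosis" (below 18 mmol/L, against moderate acidosis), "and for previous alkali treatment (yes/no"). The allocation rule is strong: "We use the minimization method with a preferred treatment probability of 0.9, and a combination depth of 2.0". Its stated purpose is "to guarantee that treatment allocation is balanced in all levels of the stratification factors, as well as in all pairwise combinations of stratification factors".

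Under Statistical methods, three models have explicit covariate lists:

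- **Primary longitudinal eGFR model:** "all stratification criteria (age, diabetes, severity of acidosis, previous alkali treatment"), together with baseline eGFR, time, and treatment by time.
- **Time to RRT, with death as a competing risk:** "including treatment group and the covariates age, diabetes, severity of acidosis and baseline eGFR".
- **Percent change in bone markers (ANCOVA):** sex, age, the change in kidney function over the interval, and the baseline marker values.

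The article gives no reason for the different sets. Under Outcome parameters, both RRT and the bone markers are secondary.

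**The concern.** Minimisation at this strength removes most of the chance imbalance between arms on the four factors. If one of them predicts the outcome, part of the outcome variance can no longer contribute to the treatment difference. A linear model that leaves the factor out still counts that variance in its residual. It therefore reports a standard error larger than the design warrants, and its test rejects less often than its nominal level.

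The article's own reasoning makes some omitted factors plausible predictors. The Background states that acidosis affects bone metabolism, yet acidosis severity is left out of the bone-marker model. Patients already on alkali enter only after a 4-week wash-out, so those counted as previously treated may differ in later course from those who were not.

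At stake are some power and honest confidence-interval width for the bone markers. For RRT, what is at stake is whether the adjusted effect is conditional on the same factors as the allocation and the primary analysis. These are stated lists, not details left to a later plan, so the inconsistency is in the article itself.

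**Working it through.** **Step 1. Compare the lists.** The article gives no figure on this point. Its one sample-size calculation concerns eGFR and does not enter here.

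| Factor used in minimisation | Primary eGFR | RRT | Bone markers |
|---|---|---|---|
| Age | yes | yes | yes |
| Diabetes | yes | yes | no |
| Acidosis severity | yes | yes | no |
| Prior alkali therapy | yes | no | no |
| **Count** | **4 of 4** | **3 of 4** | **1 of 4** |

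**Step 2. Size in the linear ANCOVA, by formula.** Let R² be the share of the ANCOVA's residual variance that the omitted factors explain, and suppose they are exactly balanced. The treatment difference then has (1 − R²) times the variance the model reports. The reported standard error is too large by 1/√(1 − R²), and the true two-sided error at nominal 5% is 2 × [1 − Φ(1.96/√(1 − R²))]. R² is an assumption, as the article gives no value.

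- R² = 0.05: 1/√0.95 = 1.026; 1.96 × 1.026 = 2.011; true error 4.4%.
- R² = 0.10: 1/√0.90 = 1.054; 1.96 × 1.054 = 2.066; true error 3.9%.

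**Step 3. Check by simulation.** Inputs from the article: 200 patients, four binary factors, minimisation with probability 0.9 on the factors and their six pairwise combinations. Assumptions: prevalences of 50% (older age group), 35% (diabetes), 25% (severe acidosis) and 30% (prior alkali therapy); age explains 5% of outcome variance; the three omitted factors share the rest of the explained variance equally; the effect for power is 0.4 SD. There were 2,500 simulated trials per setting. Simulation error is √(0.05 × 0.95/2500) = 0.4 points for type I error and about 0.7 points for power.

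| Outcome variance explained by the three factors | Type I error, age only | Type I error, all four | Power, age only | Power, all four |
|---|---|---|---|---|
| 0% | 5.6% | 5.7% | 83.3% | 83.3% |
| 5% | 4.8% | 5.2% | 82.3% | 83.4% |
| 10% | 4.2% | 5.0% | 85.6% | 88.1% |
| 20% | 2.5% | 4.7% | 84.6% | 89.9% |
| 30% | 2.0% | 5.7% | 87.1% | 93.8% |

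Power should be compared within a row only, because residual variance falls down the table. At 10% or less the loss is small. It becomes marked only at 20–30%, and nothing in the article supports strengths of that order.

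**Step 4. The RRT model.** Steps 2 and 3 apply to a linear model. In a hazard-type regression on the cumulative incidence, adding a prognostic covariate generally does not shrink the standard error of the treatment coefficient. It changes the conditional effect being estimated, usually moving it away from the null. The figures above therefore do not carry over. The model now has five terms (treatment, three factors, baseline eGFR) and would have six. The expected number of RRT events is not stated.

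**The case against.** The best defence is that little is lost. The direction is conservative, there is no bias in the linear model, and the primary analysis already carries all four factors. This stands, and it caps the importance of the point.

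The omitted factors may also be weak once other terms are in. The ANCOVA adjusts for the marker's value at day 0, which for previously treated patients falls after wash-out and may absorb much of their difference. Prior alkali therapy is defined narrowly (more than 6 months, with bicarbonate at or above 20 mmol/L on over 75% of measurements), so the positive group could be small. This also stands: the gain may be near zero.

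For RRT, a short list could be defended if events are few. The article does not make that argument, and it would not explain the ANCOVA, where three binary terms among about 200 patients are easily supported.

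Three stronger readings are tempting and are not supported:

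- A reader might infer that the RRT standard error is too large for the same reason as in the ANCOVA. That argument belongs to linear models.
- A reader might treat RRT as the trial's main clinical outcome. The article lists it as secondary, beside death.
- A reader might convert the ANCOVA loss into patients: 200/(1 − R²) − 200 gives 11 at R² = 0.05 and 22 at R² = 0.10. This rests on an assumed R² and overstates the true loss of precision, because minimisation already gives the point estimate most of the benefit. Omission mainly inflates the reported standard error.

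The ANCOVA also adjusts for a change in kidney function measured after randomisation. That is a separate matter, which adding baseline factors does not settle.

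**Conclusion.** The inconsistency is real and can be read directly from the text: four of four factors in the primary model, three in the RRT model, one in the bone-marker ANCOVA, with no reason given. For the ANCOVA the consequence is a conservative test and an inflated reported standard error, without bias. The size depends on prognostic strengths and prevalences that the article does not give. With an assumed 10% of outcome variance in the omitted factors, it is under one point of type I error and about 2.5 points of power (88.1 − 85.6). For RRT, the case is alignment with the randomisation factors and clarity about the conditional effect; no gain in precision is claimed. Nothing is claimed about the time-to-death part of the joint model, whose covariates are not stated. Since both outcomes are secondary, this is a minor improvement and not a threat to the trial's conclusions.

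**What to change.** Add diabetes, acidosis severity and prior alkali therapy to the bone-marker ANCOVA. This costs three parameters among about 200 patients.

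Add prior alkali therapy to the RRT model, so that it carries all the minimisation factors along with baseline eGFR. This costs one parameter in a model whose event count is unknown. If the expected number of events is judged too small for it, keep the shorter list and state that reason.

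All four factors are recorded at randomisation, so no new data are needed. In an open-label trial, the change should be fixed before outcomes are compared by arm, so that the covariate choice cannot appear to have followed the results.

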## Background

Chronic kidney disease (CKD) occurs in approximately one in ten persons worldwide and represents not only a medical challenge but also a great socioeconomic burden. Major efforts have been made to investigate treatment options aiming to slow progression to end-stage renal disease (ESRD) and, subsequently, to reduce mortality in kidney patients. A renin-angiotensin system blockade with either angiotensin-I-converting enzyme inhibitors or angiotensin-II-receptor antagonists slows the progression of decline in renal function [1-5]. However, further therapeutic interventions have not shown any benefits [6-10]. The comprehensive summery by Fink *et al.* underscores the lack of evidence-based treatment concepts in CKD and even calls screening and monitoring for early-stage CKD into question [11].

Overt chronic metabolic acidosis in CKD patients develops after a drop in glomerular filtration rate (GFR) to less than approximately 25 mL/min/1.73 m^2^. The pathogenic mechanism seems to be a lack of tubular bicarbonate production, which in healthy individuals neutralizes the acid net production. As shown in several animal and human studies the acidotic milieu alters bone and vitamin D metabolism [12], induces muscle wasting [13], and impairs albumin synthesis [14], in addition to other detrimental effects [15,16]. Experiments in rats suggest that even in the earlier stages of CKD with serum bicarbonate levels within normal limits, increased per-nephron acidification occurs to obviate overt metabolic acidosis [17]. Investigations to elucidate the contribution to the progression of CKD itself have provided contradictory results [18-20]. However, there is evidence that the alternative complement system is activated by increased tubular ammonia production [21] and that endothelin, angiotensin II and aldosteron kidney concentrations are increased as a direct result of distal nephron acidification [17,20,22]. Taken together, these alterations induce tubulointerstitial scarring in the long term.

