The results of several retrospective studies conducted in different types of populations showed clear associations between acid–base imbalance and increased mortality [23,24]. Above all is the recently published analysis of the CKD registry of the Cleveland Clinic health care provider in 41,749 patients with CKD stage III and IV (estimated (e) GFR of 60 to 15 mL/min/1.73 m^2^, measured by the Chronic Kidney Disease Epidemiology Collaboration equation). Adjusted for several covariates the all-cause mortality for subjects with a low serum bicarbonate level (<23 mmol/L) is 23% higher than for those with a level within the normal range (23 to 32 mmol/L) [25].

The first prospective studies in closely selected study populations [26] using various therapeutic interventions [27] and endpoints revealed beneficial effects. In particular, de Brito-Ashurst *et al.* showed that sodium bicarbonate supplementation in patients with CKD stage IV slows the decline in renal function, although the study comprised some serious methodological limitations [28].

In line with the aforementioned studies we assume that a sufficiently balanced acid–base status leads to a reduction in the decline of renal function in patients with CKD. Bicarbonate is necessary to counterbalance acid net production arising from protein metabolism and acid-rich diets. Thus, the intervention of exogenous bicarbonate supplementation to substitute the lacking endogenous bicarbonate would appear to be rational. This simple concept has existed for a long time, but has never been investigated sufficiently to state clear treatment guidelines for physicians. Furthermore, including patients with both moderate and severe grades of renal impairment represents a novel and comprehensive approach. Thus, conclusions drawn by results of this study are directly applicable to routine care and treatment guidelines.

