### Outcome parameters

The primary outcome is renal function and will be measured by means of eGFR, calculated according to the 4-variable-MDRD Study equation [36].

Secondary outcomes are death, and the need for renal replacement therapy (RRT) (patients with renal transplantation, hemodialysis, peritoneal dialysis, and subjects who are in need of RRT, but personally elect not to start it). The need for RRT will be clinically evaluated, including monitoring of uremic symptoms (nausea and/or vomiting, fatigue, deterioration in nutritional status and significant weight loss, neuropathy, encephalopathy, or psychic disturbances), blood and fluid disturbances (volume overload, malignant hypertension, anemia, bleeding diathesis, pleuritis and/or pericarditis), and significant electrolyte imbalances. A further secondary outcome is the percent change in markers of bone metabolism (bone alkaline phosphatase, osteocalcin, c-telopeptide pyridinoline crosslinks of type I collagen, and procollagen type I N-propeptide) across groups.

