### Sample size

Assuming equal baseline levels of eGFR between the two study groups, a clinically relevant difference of 5 ml in eGFR after 2 years, and an estimated standard deviation of 12 ml for the change in eGFR after 2 years (pilot data, Figure 2), an independent sample *t*-test with a sample size of 2 × 100 patients will give 80% power to reach statistical significance at a two-sided significance level of 5%.

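### The bone-marker ANCOVA adjusts for change in renal function, a post-randomisation variable that treatment is expected to change, so it does not estimate the total randomised effect on bone

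*Protocol article*

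**What the plan says.** Under Outcome parameters, the protocol article names the bone markers as a secondary outcome: "A further secondary outcome is the percent change in markers of bone metabolism". Under Statistical methods it sets the two intervals, "Percent change (from baseline to week 20 and baseline to week 104, respectively) in markers of bone metabolism", and says that these "will be analyzed by analysis of covariance, to adjust for sex, age, change in renal function, and baseline values of the bone markers". The third covariate is the one at issue.

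Three other places show what that covariate is:

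- Outcome parameters: "The primary outcome is renal function and will be measured by means of eGFR".
- Background: the trial assumes that a balanced acid–base status "leads to a reduction in the decline of renal function in patients with CKD".
- Sample size: the trial is planned on "a clinically relevant difference of 5 ml in eGFR after 2 years".

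The article gives no reason for including the covariate, does not call the model a direct-effect, mediation or sensitivity analysis, and describes no version without it. In the same section, the mixed model for the primary outcome and the competing-risk model for renal replacement therapy (RRT) both adjust for eGFR at baseline, not for its change.

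**The concern.** An ANCOVA in a randomised trial estimates the effect of assignment when its covariates are fixed before treatment can act. Change in eGFR is not fixed in this way. On the trial's own hypothesis, treatment moves it.

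Conditioning on it does two things. First, it takes out of the treatment coefficient whatever part of the bone effect passes through kidney function. Second, it compares patients who reached the same eGFR change under different treatments. Such patients are no longer exchangeable if something unmeasured drives both eGFR decline and bone turnover, so a difference can appear where treatment has no effect on bone.

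The article also describes a route to bone that need not pass through eGFR, since "the acidotic milieu alters bone and vitamin D metabolism". The total effect may therefore combine a direct and a mediated part, and the planned model mixes up which of these is reported. A real effect could be understated, or a spurious one reported, for a named secondary outcome.

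**Working it through.** **1. The plan's own figure.** The article states no power, SD or effect size for the bone markers. Its only power figure is for eGFR: 80% with 100 per arm, difference 5 mL, SD 12 mL, two-sided 5%. Recomputed: 5/(12 × √(2/100)) = 2.95, and Φ(2.95 − 1.96) = 83.8% (83.4% with the exact t distribution). The stated 80% is on the conservative side and has no bearing on this point. The 5 mL and 12 mL are used below.

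**2. What the covariate does to the coefficient.** Let Δ be the between-arm difference in eGFR change and b the within-arm slope of marker change on eGFR change. Then:

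adjusted coefficient = total effect − b × Δ.

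In SD units of marker change, the shift b × Δ equals r × Δ/SD(eGFR change), where r is the within-arm correlation. If r is causal, the shift is the mediated effect that has been removed. If r reflects a common cause, the shift is bias.

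**3. Week 104.** Δ/SD = 5/12 = 0.417. The article gives no r, so 0.2 to 0.5 is an assumption:

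- r = 0.2: 0.2 × 0.417 = 0.083 SD
- r = 0.3: 0.3 × 0.417 = 0.125 SD
- r = 0.5: 0.5 × 0.417 = 0.208 SD

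**4. Week 20.** No week-20 difference or SD is given. If the difference builds up linearly, it is 5 × 20/104 = 0.96 mL. With SD still 12 mL, Δ/SD = 0.080, and r of 0.2 to 0.5 gives 0.016 to 0.040 SD. Only if the SD shrank in proportion to time would the week-104 range carry over. This takes the eGFR change over the same interval as the marker change.

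**5. Simulation.** Inputs: 100 per arm, eGFR change with difference 5 and SD 12, assumed residual SD of 30 percentage points for marker change, 3,000 trials per setting. Effects are in percentage points.

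| Setting (assumed) | Without eGFR change: estimate, rejection rate | As planned: estimate, rejection rate |
|---|---|---|
| Direct effect −5, marker moves −1 point per mL | −10.0, 59% | −5.0, 22% |
| No direct effect, marker moves −1 point per mL | −5.0, 19% | about 0, 5% |
| No bone effect, shared cause with variance fraction 0.2 | about 0, 5% | −2.6, 9% |
| No bone effect, shared cause with variance fraction 0.4 | −0.1, 5% | −5.1, 25% |

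These agree with step 2. In the first two rows b × Δ = −1 × 5 = −5, which is the part lost. In the last two rows r equals the shared fraction, so the expected bias is 0.2 × 5/12 × 30 = 2.5 and 0.4 × 5/12 × 30 = 5.0 points in size.

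If neither mediation nor a shared cause is present, the covariate does almost no harm: with a direct effect of −10 only, both models estimate about −10.0, with power 65% and 62%.

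**The case against.** The best defence is that kidney function itself affects bone turnover, so the investigators may want the bone effect of bicarbonate over and above any effect on eGFR. That is a fair question, but a different one from the between-group comparison of the secondary outcome. Its answer also needs the assumption that nothing unmeasured drives both eGFR change and marker change. The article neither poses that question nor labels the model accordingly.

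It is also fair to say that the sizes above rest on assumed marker inputs, that they are illustrated mainly at week 104, and that this is one covariate in one secondary analysis. All of that stands and limits how serious the point is.

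A reader might infer more, and the document does not support it:

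- **That percent change as the outcome loses power.** The article gives no distribution, SD or baseline correlation for the markers, and the ANCOVA already includes the baseline marker. With assumed log-normal markers (log SD 0.3 to 0.7, correlation 0.5 to 0.85), the loss against a log-scale ANCOVA is about 1 to 18 points. Against a raw-scale ANCOVA, percent change runs from about 5 points worse to about 13 points better. The scale is a consistent, pre-specified choice.
- **That patients who die or start RRT drop out of the model differently by arm because of this covariate.** No differential rate is given. A patient who dies before week 104 has no marker value at that time either, so removing the covariate would not bring that patient back. Nothing says that RRT patients are excluded or lack an eGFR value.
- **That the intention-to-treat principle is abandoned.** The article says "The intention-to-treat population will be used for statistical analysis". The fault is in what the coefficient estimates, not in who is analysed.

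**Conclusion.** The point holds for the covariate. As written, the bone-marker model conditions on a post-randomisation variable that the trial expects treatment to change, so its treatment coefficient is not the total randomised effect on bone. At best it is a direct effect, and only if there are no unmeasured common causes.

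That conclusion follows from the text alone. The size does not: 0.08 to 0.21 SD removed at week 104 assumes that the planned 5 mL difference occurs, that the SD is 12 mL, and that a correlation of 0.2 to 0.5 is causal. The effect at week 20 is probably smaller, and the distortion grows with the drug's effect on eGFR.

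This should be fixed, but it is not critical. The primary analysis and the analyses of death and RRT do not use this covariate.

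**What to change.** In the bone-marker sentence of Statistical methods, delete change in renal function. Adjust for baseline quantities only: baseline marker, sex, age, baseline eGFR and the stratification factors (age, diabetes, severity of acidosis, previous alkali treatment). Baseline eGFR brings this model into line with the primary and RRT models.

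If the effect on bone not explained by eGFR is of interest, keep the change-adjusted model as an explicitly labelled exploratory direct-effect analysis, with its no-unmeasured-common-cause assumption stated.

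Percent change can remain the outcome. A log-scale analysis is at most an option and is not needed to correct this fault.

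The cost is a change of analysis wording. No new data, visits or patients are needed.
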